## METHODS

### Study organization

The study is based on a collaboration between Aga Khan University, Tanzania, the non-governmental organization ‘Comprehensive Community Based Rehabilitation in Tanzania’ (CCBRT), University of Copenhagen, Denmark and VU University of Amsterdam, the Netherlands. The study team includes five PhD students and two postdocs with support from senior researchers and trained research assistants. The researchers’ backgrounds cover clinical obstetrics and midwifery, social sciences, implementation science, epidemiology, statistics, and health economics.

Since 2010, CCBRT has supported maternal and perinatal health care in 22 of Dar es Salaam’s health facilities, including the study sites, through training, infrastructure upgrades, and data strengthening initiatives [33]. Thereby, CCBRT will play a major role in data collection and facilitation of close collaboration with the hospitals’ administrations, the district medical officer and the regional administrative office for health.

The advisory board, which includes representatives from the Tanzanian Ministry of Health and international experts, will oversee study methodologies and alignment with national guidelines and policies. The advisory board will also assist in bridge-building for policymakers and other stakeholders.

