##### Evaluation of direct health outcomes

Our primary direct health outcomes are perinatal survival (stillbirths with positive foetal heart upon admission and pre-discharge neonatal mortality during the first seven days among inborn babies weighing ≥1000 g) and potentially avoidable CSs (by criterion-based case file review of care preceding surgery). Our secondary direct health outcomes include additional perinatal indicators (perinatal deaths divided into 1000–1999 g and ≥2000 g, first 24 hours pre-discharge neonatal mortality, Apgar score <7, admission to neonatal intensive care unit), maternal indicators (death, postpartum haemorrhage, uterine rupture, postpartum hysterectomy), and mode of birth (spontaneous vaginal birth, vacuum extraction, CS). In addition, background characteristics will be recorded for all women (age, parity, previous perinatal death, date and time of admission and birth, and birthweight). Sociodemographic indicators such as marital, economic, and educational status are not available in birth registries.

Birth outcomes and mode of birth will be prospectively measured from baseline and until nine months after the PartoMa intervention is implemented in the last facility. Thus, data collection will be ongoing for 18 months (Figure 3). Data will be gathered twice a week on each of the five study sites, primarily from the intrapartum birth register. Key indicators will be cross-checked with the antenatal, surgical, neonatal and postnatal wards registers and with the death certificate counter book. For each study site, data will be double entered every fifth week to ensure that the accuracy of data retrieval remains above 95%. Women referred to the study sites prior to birth from non-study health facilities will be included, but their clinical care prior to admission will not be possible to assess. When referrals occur from one to another study site, data will be recorded on where the woman gave birth. Babies referred postpartum for intensive care will be recorded at the facility where the woman gave birth (Table 1).

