##### Evaluation of quality of care (QoC)

Quantitative assessments of potential changes in the QoC during birth are divided into provision and experience of care [51], with sample size calculations based on findings from the situational analysis.

For care provision, a criterion-based audit of case files will be conducted at each facility during three baseline months and the 7^th^-9^th^ implementation months (Figure 3, Table 1). This analysis is limited to intrapartum management preceding CSs, including the rate of potentially avoidable CSs, and intrapartum management of severe hypertensive disorders. These focus areas suit our preliminary assessments of data availability and accuracy in case files. Moreover, they represent a major challenge in reaching beyond the co-existence of TLTL and TMTS care to save lives [9]. Within the pre- and post-intervals at each study site, all case files will be assessed during the weekly data collection to retrieve case files of: i. women giving birth by CS; and ii. women suffering from severe hypertensive disorders (systolic BP ≥160 and/or diastolic BP ≥ 110 and/or eclampsia) (Figure 3, Table 1). Both the analysis of potentially avoidable CSs and the analysis of severe hypertensive disorders will be based on audit criteria, which were previously successfully applied in Tanzania [25,52,53]. Notably, indicators and methods for auditing case files might be further modified based on the final results of the situational analysis.

To assess potential changes in women’s experiences of care, women will be invited to respond anonymously to a validated, structured questionnaire through phone calls 2 to 4 weeks after birth. Compared to interviews before discharge where women have yet to reflect on their experiences, this timeframe has previously proven relevant in the Dar es Salaam context to ensure adequate reporting [54]. In each facility, the assessment will be conducted during the three baseline months and the 7^th^-9^th^ implementation months. The questionnaire is developed based on a qualitative participatory approach consisting of iterative rounds of feedback from local and international stakeholders [37,38,55]. The main focus areas are overall satisfaction with care and occurrences of disrespect and abuse [32].

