### Data analyses

Overall analyses of the situational findings, co-creation, and implementation processes and effectiveness rely heavily on mixed-methods evaluation. This will include a broad spectrum of designs, from sequential explanatory and exploratory methods to embedded and converging triangulation designs [61].

Concerning the quantitative components, descriptive analyses will be performed in all five facilities as cluster-units of analysis. QoC provision and experience indicators (pre-selected, non-ambiguous criteria) and birth outcomes will be analysed and compared both within and between facilities using mixed effects logistic regression. Differences in seminar attendance and seminar return rates between maternity units will be compared using logistic regression. Knowledge scores are modelled as longitudinal data and compared over time using linear mixed-effects regression. Effects on each outcome will be reported as an average effect across facilities and its significance will be determined by likelihood ratio tests. Possible differences in effect between facilities will be investigated by incorporating a random slope regression model, reported by its standard deviation along with facility-specific deviations from the total effect. Possible time-dependence of the intervention (e.g. delayed entry) is investigated by allowing its effect to depend on facility-specific time since implementation and by adjusting for seasonality patterns. Additional adjustments for covariates will also be performed, such as for staff and patient counts, availability of essential supplies, other competing interventions or unintended events in the facilities, national holidays, maternal characteristics, and referral patterns. Both unadjusted and adjusted results will be reported. A biostatistician in the study team will closely supervise statistical analyses. All summary statistics and effect sizes will be reported along with 95% Wald-based confidence intervals, and statistical significance will be set at 5% level.

The qualitative analysis plan is presented separately [32].

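### Potentially avoidable caesarean, a primary outcome, is audited in pre and post windows that never overlap, and none of the described checks tests whether files are rated alike in both

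*Protocol article*

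**What the plan says.** The protocol article, under Evaluation of direct health outcomes, names two primary outcomes. One is perinatal survival. The other is "potentially avoidable CSs (by criterion-based case file review of care preceding surgery").

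The section Evaluation of quality of care (QoC) gives the timing: "a criterion-based audit of case files will be conducted at each facility during three baseline months", and again in months 7 to 9 of implementation. The caption of Figure 3 repeats this. The retrieval step follows: "Within the pre- and post-intervals at each study site", "all case files will be assessed during the weekly data collection to retrieve case files of" CSs and severe hypertensive disorders.

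On the criteria, the same section relies on "audit criteria, which were previously successfully applied in Tanzania", and Data analyses refers to "QoC provision and experience indicators (pre-selected, non-ambiguous criteria"). The QoC section also says that "indicators and methods for auditing case files might be further modified based on the final results of the situational analysis".

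The quality checks described are register cross-checks and a five-weekly double entry for accuracy of data retrieval (Evaluation of direct health outcomes). Key Methodological Strengths and Limitations adds triangulation, improvement of routine data before the trial, and double entry as far as resources permit.

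**The concern.** Someone has to read the notes, turn them into audit items and assign each CS to a class. If this is done at each site during the windows, as the text places it, all baseline files are handled before any post file, in a setting where site and period are evident. The same file could then be read or rated differently early and late in the trial, through growing familiarity with the criteria, revised habits or expectation.

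A stepped wedge normally gives some protection, because treated and untreated sites are observed in the same calendar period. If this outcome has no such overlap, a change in rating and a change in care look the same. At stake is whether a significant result on a primary outcome can be read as a change in care.

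**Working it through.** **The plan's own figure.** No sample size or power is given for this outcome; QoC sample sizes are deferred to the situational analysis. The only power statement (80% at RR 0.78) concerns intrahospital perinatal deaths. It cannot be rebuilt without the block counts in Supplementary file S1, and it does not bear on this point.

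**Step 1: calendar of the windows.** Inputs: three clusters at three-month steps and nine further months after the third (Intervention implementation and evaluation); 18 months of data collection in total (Evaluation of direct health outcomes).
- Third roll-out: 18 − 9 = 9 months elapsed, so month 10. The earlier roll-outs are months 7 and 4.
- Implementation months 7 to 9 therefore fall in calendar months 10–12, 13–15 and 16–18.
- Baseline is months 1–3 at all sites or, at the latest, the three months before each roll-out: 1–3, 4–6 and 7–9.
- The latest pre month is 3 or 9; the earliest post month is 10. No calendar month holds both pre and post files.

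**Step 2: what a model can separate.**
- With categorical periods, the intervention indicator is the sum of the post-period indicators. The design matrix has rank 6 with and without it (cluster effects included), so the effect is not estimable.
- With a linear trend and cluster effects, the rank is 5 with the intervention term against 4 without it under a common baseline, so the effect is estimable if the trend is linear.
- With staggered baselines, post follows pre by nine months in every cluster. The rank is 4 against 4, so the effect is not estimable.

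**Step 3: size of shift that matters.** Births per window: about 60,000 a year (Abstract) / 4 = 15,000. The CS rate at the sites is not given. The 12% urban population rate (Study setting) is used as the low end; 20% and 30% are assumptions. Files per window: 15,000 × 0.12 = 1,800; × 0.20 = 3,000; × 0.30 = 4,500. The baseline avoidable share among CSs is assumed to be 20%, 35% or 50%, and the test two-sided.

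For a drop d from p, with p̄ = p − d/2, solve d / √(2p̄(1 − p̄)/n) = 1.96. Example: n = 3,000, p = 0.35, d = 0.0239 gives p̄ = 0.338, SE = √(2 × 0.2238/3,000) = 0.0122 and z = 1.96.

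Smallest drop reaching p<0.05, in percentage points, ignoring clustering:

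| Files per window | 20% avoidable | 35% | 50% |
|---|---|---|---|
| 1,800 | 2.55 | 3.08 | 3.26 |
| 3,000 | 1.99 | 2.39 | 2.53 |
| 4,500 | 1.63 | 1.96 | 2.07 |

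This is between about 1 file in 61 and 1 in 31. At 35% avoidable and no change in care, a uniform 3-point shift is significant with probability 0.48, 0.69 and 0.85 at the three file numbers.

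A 3-point shift needs only a modest change in rating. If 35% are truly avoidable, sensitivity 0.90 and specificity 0.90 give 0.35 × 0.90 + 0.65 × 0.10 = 0.380. Sensitivity 0.85 and specificity 0.92 give 0.35 × 0.85 + 0.65 × 0.08 = 0.3495.

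**Step 4: a conservative check by site.** Paired t-test on five site differences, simulated at 35% avoidable. Probability that drift alone is significant:

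| Drift | Between-site SD of drift | 1,800 | 3,000 | 4,500 |
|---|---|---|---|---|
| 3 points | 0 | 0.32 | 0.47 | 0.63 |
| 3 points | 2 points | 0.23 | 0.34 | 0.41 |
| 5 points | 0 | 0.67 | 0.88 | 0.96 |
| 5 points | 2 points | 0.57 | 0.71 | 0.80 |

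Allowing for five sites lowers the risk but does not remove it.

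**The case against.** The strongest reply is that the weekly sentence describes finding files, not rating them; that the article never says the auditors know the period; and that masking, rating order and second raters are routinely left to a full protocol or audit manual. All of that is true, and silence on masking is not the point raised here. What stands is the stated timing: the audit is placed at each facility in the two windows, which, if followed, means time-ordered review.

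Second, the criteria are described as pre-selected and unambiguous and have been used in Tanzania before. This narrows discretion at classification. It does less for extraction, where free-text notes become audit items, and the article leaves indicators and audit methods open to change.

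Third, mode of birth is recorded from registers for all 18 months without any avoidability rating, so the total CS rate gives a partial outside check. It cannot show whether the avoidable share was rated consistently.

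Four stronger readings are tempting and are not supported:
- That the partner organisation rates the CSs. The article says only that "CCBRT will play a major role in data collection".
- That drift will occur, or will favour the intervention. No evidence of either is given.
- That rating drift can never be separated from the effect. With a common baseline and an assumed linear trend it can.
- That a null result would reliably turn significant. A 5-point shift at a 50% share and 1,967 files (13,116 × 5/4 × 0.12) gives 0.05/√(2 × 0.25/1,967) = 3.1, but the shift and the share are both assumed and clustering is ignored.

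**Conclusion.** The concern holds in a limited form. For this primary outcome the pre and post windows do not share a calendar month, so a change over time in reading or rating files falls on the intervention contrast unless a trend shape is assumed. The seasonality and covariate adjustments in Data analyses do not measure rating, and the described checks concern retrieval and registration.

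Under the assumed 1,800 to 4,500 files per window and 20% to 50% avoidable, a shift of roughly 2 to 3 points (1.6 to 3.3 at the extremes) could reach p<0.05 ignoring clustering. More would be needed with a random slope, with drift that differs between sites, or with a smaller audit sample. Site CS rates, avoidable shares and the audit sample size are not in the article, so these figures illustrate scale and do not predict bias. The change below is worth making before baseline files are rated. If a fuller document already provides it, a sentence saying so would settle the point.

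**What to change.** 1. Lock the audit criteria before the first baseline file is audited. Changes prompted by the situational analysis should be complete by then.
2. Keep weekly retrieval. Record only the raw items found in the notes, on a form that carries no avoidability rating.
3. After the last window closes, remove site, date and provider from the forms and classify all CSs in one randomly mixed pre/post order, or by a fixed algorithm where the criteria allow.
4. Re-extract from the notes and re-classify a small sample of files from both windows, for example 5% to 10%, and report agreement by period. With 3,600 to 9,000 files over both windows (2 × 1,800 to 2 × 4,500), 5% is 180 to 450 files and 10% is 360 to 900. Repeating the extraction matters, because first extraction remains in time order and is where discretion persists under explicit criteria.

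The cost is a redesigned form, some extra work for existing staff, and later results for this outcome. Masking will be imperfect where the notes themselves reveal the period. The change deals with rating consistency only. It does not remove secular trend, which is a separate limitation of non-overlapping windows and should be stated as such.

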**Workload***(patient volume; numbers, composition and organization of providers; provider-to-labouring women ratios)* **Management /leadership structure** **Infrastructure and supplies***(physical organization of maternity units, essential medication, monitoring devices, birth equipment, disinfection facilities, personal protective equipment)* **Other ongoing interventions***(e.g. training, supervision, clinical practice guidelines, construction)* **Data quality***(registration of clinical assessments, maintenance and use)* **Referral systems**	**Clinical surveillance** Admission assessment *(history and physical assessment)* Partograph use Foetal wellbeing *(by foetal heart auscultation)* Labour progression *(by recordings of cervical dilatation and membranes)* Maternal vital signs *(blood pressure, pulse rate, temperature)*	**Intrapartum treatment** Caesarean section *(divided into medically indicated and potentially avoidable)* Prolonged labour *(incl. timely and safe use of artificial rupture membranes and oxytocin)* Severe hypertensive disorders *(incl. timely use of antihypertensives and magnesium sulphate)*	**Caring support** Communication *(incl. verbal and physical abuse)* Birth companionship and emotional support Respect and preservation of dignity *(e.g. privacy)* Pain relief Mobilization and birth position User fee structure	**Primary outcomes** Perinatal survival *(intra-hospital stillbirths, pre-discharge neonatal deaths within 7 days)* Potentially avoidable caesarean sections *(by assessment of care before caesarean section)* **Secondary outcomes** Perinatal outcomes *(perinatal deaths divided into 1000–1999 g and ≥2000 g, neonatal first 24 hours pre-discharge mortality, Apgar score <7 and <9, admissions to neonatal intensive care)* Maternal outcomes *(death, postpartum haemorrhage, perineal tear, uterine rupture, postpartum hysterectomy)* Mode of birth *(spontaneous vaginal birth, vacuum extraction, caesarean section)*

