## Key Methodological Strengths and Limitations

This PartoMa Scale-up Study directly addresses the urgent need for research on co-creation, implementation, and scale-up of context-specific CPGs in overstretched, high-volume maternity units in LLMICs [9,22,30]. We have not identified any similar studies.

We developed a pragmatic study design, aiming to produce an extensive description of context, intervention co-creation, and implementation strategy, and include a broad range of process, outcome and economic measures. Such a broad, real-world scale-up may enable an in-depth understanding of how the intervention might achieve impact and may be sustained or translated from one context to another. It, however, also entails inherent trade-offs, of which the most central are presented here [63]:

First, a dilemma arose in deciding the degree to which the intervention can be allowed to vary across the five sites, with limited resources and at the expense of statistical rigor. Unimodal, non-complex interventions do not typically produce lasting changes in complex health-care systems, and we aim to enable flexibility and creativity in the intervention co-creation [63]. However, as we hypothesize co-creation to be highly resource consuming for each single maternity unit in LLMICs, and as health providers are often shifted between the facilities, we plan for one version of the intervention for all five sites, but with some flexibility in implementation plan between sites [22]. In addition, this balance between fidelity and adaptation aims to strengthen the overall trial design, which, if the intervention proves effective, may strengthen the advocacy process for adoption and further scale-up by the government (33). By comparing quantitative and qualitative results between study sites, we may explore potential issues regarding this approach.

Second, low-quality data may influence validity. We have designed a study to overcome this challenge by: *i*. ensuring multiple indicators and research methods at each level of evaluation and thereby the possibility of triangulation; *ii*. exploring routine data monitoring during the situational analysis, which allows measures to be taken to improve the quality of data prior to the trial; *iii*. prospectively collected birth outcome data will be cross-checked regularly; and *iv*. double-entry of data will be applied to the extent resources allow.

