**Table ut0001:** 

**Box 1** The PartoMa pilot intervention in Zanzibar, consisting of pocket booklets with locally co-created guidelines on common care during birth and associated quarterly recurring seminars, where the guidelines are practiced in groups passing through five stations. In Zanzibar’s tertiary hospital, a pre-post study suggested that the multifaceted PartoMa intervention appeared associated with a 33% decrease in stillbirths and halving in babies with low Apgar score. The intervention follows a ‘self-directed approach’ where use of the guidelines and participation in seminars are voluntary and based on inner motivation. At each seminar station, locally realistic case stories are discussed, based on partographs and both routine and emergency care during birth, respectful support, triage, and hands-on training are included. The Zanzibar PartoMa guidelines are available online (publichealth.ku.dk/partoma). *Photos by [name], [name] and [name]. All identifiable people have given their oral consent*.

Finally, a challenge arises if the success of the implementation is highly different across sites, which may leave the overall results of the stepped-wedged trial inconclusive. In this case, the theory-based, mixed-methods study design will allow us to conduct in-depth analyses focused on individual effects at hospital level, which can be compared across sites. This flexibility to assess intra- and inter-site variability is particularly important for addressing questions of transferability and scalability. In addition, while the current evaluation timeframe reflects our funding limitations, it may be argued that an evaluation time frame of nine to 15 months is insufficient for assessing potential long-term impact. If the intervention appears effective and continues, we aim to fundraising for additional post-exit evaluations, including in-depth exploration of long-term sustainability and potential further scale-up in Dar es Salaam and beyond.

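### Avoidable caesareans, a primary outcome, are judged only from case files that may become more complete after roll-out, and the plan does not separate fuller notes from better care.

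*Protocol article*

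**What the plan says.** The section on direct health outcomes names two primary outcomes, perinatal survival and "potentially avoidable CSs (by criterion-based case file review of care preceding surgery". The case file is the only stated source for the second.

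The quality-of-care section sets the timing: "a criterion-based audit of case files will be conducted at each facility during three baseline months and the 7^th^-9^th^ implementation months". It says that the analysis "will be based on audit criteria, which were previously successfully applied in Tanzania", and that "indicators and methods for auditing case files might be further modified based on the final results of the situational analysis".

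Recording is also close to what the trial tries to influence. Table 1 lists partograph use as a process indicator, measures labour progression "by recordings of cervical dilatation and membranes", and lists partograph skills as a provider competency. Box 1 describes pilot seminars in which "locally realistic case stories are discussed, based on partographs".

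The plan knows that records are a weak point. The limitations section says that "low-quality data may influence validity" and answers with triangulation, data-quality improvement before the trial, cross-checks and double entry. The situational analysis studies the step from clinical assessment to case-file entry. The audit topics were chosen with data availability in mind. Table 1 lists data quality as a structure indicator, and structure data are collected at every site each quarter.

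**The concern.** The two audit windows at each site are also its unexposed and exposed periods. Anything that changes how much is written down between them is therefore tied to exposure. If a caesarean is called avoidable or not partly because the file is silent, the outcome reflects two things at once: the care before surgery and the completeness of the notes.

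A primary outcome is at stake. It could show a benefit or a harm when care has not changed, or lose a benefit that is real. The perinatal outcome is not exposed in the same way, because it comes from registers that are cross-checked against other registers.

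**Working it through.** The article gives no baseline share, expected effect or sample size for avoidable caesareans, so there is no figure of the plan's to reproduce here. The stated 80% power at a relative risk of 0.78 concerns perinatal deaths. Everything below is illustration on assumed inputs.

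**Inputs (all assumed).** *p* is the true share of caesareans that are avoidable. *c* is the share of files complete enough to judge, unrelated to avoidability unless stated. The denominator is caesareans.

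**Observed share under each coding of files that cannot be judged**
- counted as avoidable: *c·p* + (1 − *c*)
- counted as not avoidable: *c·p*
- excluded: *p*

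**No true effect (same *p* in both windows), odds ratio after versus before**

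| *p* | *c* before → after | Counted as avoidable | Counted as not avoidable | Excluded |
|---|---|---|---|---|
| 0.40 | 0.50 → 0.70 | 70% → 58%, OR 0.59 | 20% → 28%, OR 1.56 | 1.00 |
| 0.40 | 0.70 → 0.80 | 58% → 52%, OR 0.78 | 28% → 32%, OR 1.21 | 1.00 |
| 0.40 | 0.80 → 0.85 | 52% → 49%, OR 0.89 | 32% → 34%, OR 1.09 | 1.00 |
| 0.20 | 0.80 → 0.90 | 36% → 28%, OR 0.69 | 16% → 18%, OR 1.15 | 1.00 |

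Second row in full: (0.52/0.48) ÷ (0.58/0.42) = 0.78 and (0.32/0.68) ÷ (0.28/0.72) = 1.21.

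**Exclusion when completeness is related to avoidability.** Let *c*ₐ and *c*ₙ be completeness among avoidable and other caesareans. The odds among retained files are the true odds times *c*ₐ/*c*ₙ, so the odds ratio is multiplied by the after-to-before ratio of *c*ₐ/*c*ₙ. With *p* = 0.40, suppose *c*ₐ = 0.60 and *c*ₙ = 0.75 before, and both are 0.80 after. Overall completeness goes from 0.24 + 0.45 = 0.69 to 0.80, and the odds ratio is (0.32/0.48) ÷ (0.24/0.45) = 1.25 with no true effect. If the relation is the same in both windows the odds ratio survives although the shares are biased, but incomplete files cannot show whether that is so.

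**True fall of 22% (0.40 → 0.312), completeness 0.60 → 0.80**
- counted as not avoidable: 0.240 → 0.2496, relative risk 1.04, so the benefit disappears
- counted as avoidable: 0.640 → 0.4496, relative risk 0.70 against a true 0.78, so the benefit is exaggerated

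**Chance of a significant result with no true effect.** Assume 1,800 caesareans per window (60,000/4 births × 12%, the population-based urban rate in the article), a two-sided 5% test and no clustering. For *p* = 0.40 and 0.70 → 0.80, the chance is 95% (apparent reduction, blanks avoidable) or 75% (apparent increase, blanks not avoidable). With 500 per window it is 48% or 28%. For 0.80 → 0.85 with 1,800 per window it is 44% or 25%. Ignoring clustering overstates these chances.

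**The case against.** The strongest reply has four parts.

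*The handling rule matters and may exist elsewhere.* A reader might infer that every way of coding unrecorded care is biased, whatever the cited criteria say. The documents do not support that: under the same simple model, exclusion gives an odds ratio of 1.00. The rule may stand in the cited audit sources or a fuller protocol. This stands, and it limits the claim to the two fixed codings, plus exclusion where completeness and avoidability are linked.

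*The rise in completeness is inferred.* A reader might also infer that fuller case files are a stated aim of the intervention. No section says so, the programme theory does not list it, and Box 1 describes the pilot version, which is to be modified. This stands too. A rise is plausible because partograph use and skills are measured as things that may change, but its size is unknown.

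*Safeguards exist.* The data-quality work is real and deserves credit. Improvement before the trial raises the starting level, the quarterly visits can show drift, and cross-checks and double entry protect retrieval and transcription. None of these decides how a silent file is classified or separates a change in recording from a change in care.

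*Recording is partly care.* The outcome is judged on care before surgery, so a file without assessments may mean that none were made. Where that is true, a change seen in the notes is partly the intended effect. This is a reason to show how much of the result rests on silent files.

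**Conclusion.** The concern holds as a cheap improvement to how a primary outcome is classified and reported. The plan relies on case files alone, compares windows that coincide with exposure, and gives no means of telling better notes from better care. With a true share of 40% and a completeness gain of 10 points, from 70% to 80%, the spurious odds ratio is 0.78 or 1.21 depending on the rule. A gain of 5 points, from 80%, gives 0.89 or 1.09.

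These sizes rest on assumed shares and completeness. They show what could happen, not that completeness will rise or that the eventual rule will be a biased one.

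A reader might conclude that an effect should be claimed only if its direction holds under both extreme codings. That goes too far. With completeness going from 50% to 70%, a true fall of 22% reads 20.0% to 21.8% (0.70 × 0.312) when blanks count as not avoidable, and a real benefit would be denied. Any true relative reduction below 1 − 0.50/0.70, about 29%, would fail that test.

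**What to change.** Before the baseline audit is classified:

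1. Add a third category, 'not judgeable from file', defined by the same minimum set of recorded audit items in both windows. The plan still leaves audit methods open to modification, so this fits.
2. Report the share of judgeable files by window and site next to the outcome.
3. Prespecify one primary coding of files that cannot be judged, and keep it.
4. Report sensitivity analyses with those files coded as avoidable, coded as not avoidable, and excluded. Temper the conclusion if the effect depends on the coding, but do not make agreement of the two extremes a condition for claiming an effect.
5. Read the result beside the caesarean rate from the birth register, which is already collected as a secondary outcome.

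The cost is one more category on the audit form, slightly more audit and analysis work, and possibly a more cautious conclusion if many files are incomplete. No additional files are needed.
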